## Abstract

**Background:**

People with migraine often experience disability with serious consequences for their social life and work productivity. The pharmacological prophylactic management of migraine is effective in reducing migraine attacks. However, many people are reluctant to use daily prophylactic medication, leading to a demand for non-pharmacological treatment options. We present the design for and discuss the feasibility of a pragmatic, randomized controlled trial on the effectiveness of a multimodal manual therapy (MT) treatment compared to usual care by the general practitioner (GP) for the prophylactic treatment of migraine.

**Methods:**

Eligible participants will be recruited in primary care using the International Classification of Headache Disorders III criteria for migraine of the International Headache Society. Participants will be randomized to either multimodal MT treatment or usual care provided by the GP. GPs will be asked to treat the usual care group according to the Dutch GP guideline for headache. The multimodal MT intervention will include manual pressure techniques, neck muscle-strength exercises and mobilization of the cervical and thoracic spine.

The trial will consist of a 12-week treatment period and follow-up measurements at 12, 26 and 52 weeks. The primary outcome measure is the number of migraine days per 4 weeks, assessed with a headache diary. Secondary outcome measures are the number of migraine attacks, medication use, disability due to headache, headache intensity, number of participants reporting a 50% migraine reduction, measurement of cervical pressure pain thresholds, presence of allodynia, endurance of cervical flexor muscles, days of absence of work and global perceived effect.

**Discussion:**

The results of the trial will show whether a multimodal MT intervention is an effective non-pharmacological treatment option for people with migraine.

**Trial registration:**

Dutch Trial Register, NL7504. Registered on 7 February 2019.

## Background

Migraine is a common and often disabling disorder with a high impact on work, household and social life [1]. The 1-year prevalence of migraine is estimated at 15%, and migraine is ranked as the seventh-highest cause of disability in the Global Burden of Disease study [1, 2]. In Europe, the total cost of migraine is estimated at 50.000 million euro a year, making migraine the most costly headache disorder [3]. Therefore, effective treatments that reduce the frequency of migraine are highly needed [4]. The prophylactic management of migraine generally consists of pharmacological treatment [4]. Prophylactic medication (e.g., propranolol, topiramate or amitriptyline) reduces migraine attacks by 50% in 50% of patients [5].

However, taking this medication has some disadvantages. Daily intake of prophylactic medication can cause side effects, such as fatigue and dizziness, which induce some patients to refuse this medication [6]. This has led to a growing demand for non-pharmacological prophylactic treatments to reduce the frequency of migraine [7].

The results of several studies in the past decades suggest that manual therapy (MT) might be an effective treatment to reduce migraine frequency and intensity. However, some of the studies had small sample sizes and lacked appropriate randomization, allocation concealment, blinding, intention-to-treat analysis and loss to follow-up. Thus, it is not possible to draw a definite conclusion on the effectiveness of MT for migraine [8]. Also, publication bias may have favoured studies with positive results. If manual therapy is an effective treatment for the reduction of migraine attacks, it may result in a reduction of the use of drugs, which have side effects, and in a reduction of impact on personal life. Therefore, rigorous, pragmatic research is needed that is in line with the International Headache Society (IHS) guidelines for controlled trials in migraine to determine the effectiveness of MT [9].

MT treatment for the management of headaches commonly consists of mobilization and manipulation of the cervical and thoracic spine in combination with specific exercises, posture corrections and myofascial soft tissue techniques [10–12]. A multimodal MT approach, including mobilization and manipulation of the cervical spine in combination with exercise, has been reported to be effective for tension-type headache [10, 11, 13].

The pathophysiological mechanism of migraine is still not fully understood, but sensitization of the trigemino-cervical complex has been suggested to play an important role [14–18]. Bartsch and Goadsby [19] showed convergence of nociceptive afferent input by cervical dorsal roots of C1–C3 and trigeminal afferent input onto second-order neurons at the trigemino-cervical complex. This convergence of cervical and trigeminal nociception is supported by the frequent clinical presentation of people with migraine who also experience pain and allodynia in the cervical and cephalic regions [20, 21]. Manual pressure on cervical myofascial structures can provoke a typical migraine headache, indicating referred pain based on the convergence of cervical and ophthalmic nociceptive afferents at the trigemino-cervical complex [22, 23].

Decreased pressure pain thresholds have been associated with sensitization. In migraine, decreased pressure pain thresholds of the upper cervical structures and the trapezius muscle are common [24, 25]. Migraine is associated with cervical musculoskeletal dysfunction such as cervical myofascial trigger points, decreased endurance of the neck flexor muscles and restricted mobility of the upper cervical spine [23, 26, 27]. A combination of manual pressure techniques on myofascial trigger points, neck muscle strength exercises and mobilizations of the cervical and thoracic spine targets to decrease cervical nociceptive input and to reduce sensitization of the trigemino-cervical complex. We hypothesize that manual therapy can reduce the frequency of migraine by decreasing the nociceptive transmission in the trigemino-cervical complex.

The objective of our randomized controlled trial (RCT) is to assess the effectiveness of a multimodal manual therapy treatment compared to usual care for the prophylactic treatment of migraine.

## Methods

This study is a single-blinded, multicentre, pragmatic clinical trial with two parallel groups assessing the potential superiority of a multimodal MT treatment over usual care by the GP. We will include a 4-week run-in period to provide accurate migraine frequency data prior to enrolment. The treatment will last 12 weeks with follow-up measurements at 12, 26 and 52 weeks (Fig. 1). The study adheres to the guidelines of the International Headache Society (IHS) for controlled trials in patients with migraine regarding inclusion criteria, outcome measurements and statistical analysis [9].

**Fig. 1 Fig1:**
[figure not shown]
Flow diagram of the trial. GP general practitioner, MT manual therapy

Parallel to the RCT we will conduct a prospective cohort study with migraine patients with a strong preference for MT treatment who do not want to be randomized. The aim of this parallel group is to explore the differences in patient characteristics at baseline between the randomized trial and the cohort study. Patient’s expectations with regard to recovery will be assessed in both studies and the relationship between expectations and effect of the treatment (i.e. the primary outcome measures) will be analysed. This information is necessary to better understand the generalizability of the study results. The participants in the cohort study will be treated with MT; treatment and measurements will be identical to the treatment procedure and measurements used in the RCT. All measurements will take place with a trained research assistant at one location. Participants will be given usual care by their own GP.

The design and protocol of the study have been approved by the medical ethics committee of Amsterdam University Medical Centres (location VUmc) and registered in the Dutch Trial Register (NL7504). The Standard Protocol Items: Recommendations for Interventional Trials (SPIRIT) Checklist for this research is presented in Additional file 1 [28]. Information on participants will be handled according to EU General Data Protection Regulations, and according to the guideline of the Central Committee on Research Involving Human Subjects (CCMO) in the Netherlands, to protect participant confidentiality. The study is monitored by the Clinical Research Bureau (CRB) of Amsterdam UMC location VUmc.

### Population

Participants will be recruited by the participating general practitioners (GPs) working in an urban area of Hoofddorp, The Netherlands. During consultation, the GP will provide oral and written information about the study and will invite the patient to participate. If the patient is interested in participating in the study and consents to providing contact details to the researcher, the GP notifies the researcher by email. The researcher will provide additional information about the study to the participant, followed by a telephone interview after 1 week to answer possible questions and check the inclusion and exclusion criteria. Information on the study will be provided by posters and folders in participating general practices and at the website of the coordinating healthcare centre.

### Inclusion criteria

Eligible participants are between 18 and 65 years of age and should have had migraine attacks for more than 1 year, according to the diagnostic criteria of the International Classification of Headache Disorders (ICHD) III [29]. A GP or neurologist should have established the diagnosis of migraine, and the frequency of attacks should be two times a month or more. Co-occurrence of tension-type headache is allowed if the participant can clearly distinguish this headache from migraine. Participants will only be included if they have concomitant neck pain between migraine attacks or during an attack. The use of prophylactic medication is allowed if migraine is stable and medication use has not changed in the last 3 months. Furthermore, participants have to be able to read and write Dutch.

Exclusion criteria are (suspected) malignancy, pregnancy, cerebrovascular disease, degenerative central nervous system diseases, medication-overuse headache, current diagnosis of depression or other severe psychiatric disease, rheumatoid arthritis, serious or systemic infection, fever or change in medication for migraine within 3 months before the study, and having received MT treatment for migraine up to 3 months prior to the start of the study.

### Data collection

Participants are asked to keep a headache diary and will be instructed on the way to report, in order to obtain baseline data for migraine characteristics, and will receive an appointment with the research assistant after 4 weeks. Headache diaries will be provided on paper. On each day, participants are able to report: no headache, tension-type headache or migraine, medication use and absence of work because of migraine. Before baseline measurement, the research assistant will check the inclusion and exclusion criteria and ask for written informed consent. Four weeks before the follow-up appointment, participants will be asked by email or telephone to start filling out a headache diary.

At all measurements, the data will be collected electronically (Castor EDC). The secured electronic program includes data validation checks and a data audit trail according to Good Clinical Practice standards. Only the researchers and the research assistant will have access to the data. Information on participants will be handled according to privacy regulations of the Amsterdam Public Health Quality Handbook (http://www.emgo.nl/kc/privacy/).

### Baseline assessment

Baseline assessment will include the registration of demographic variables (age, gender, education and profession), migraine characteristics according to ICHD III criteria, other physical complaints and chronic diseases.

Expectations regarding the effectiveness of treatment will be measured on a 7-point rating scale (range from 0 = no result to 6 = excellent result expected). Patient’s preference for treatment will be administrated (preference for usual care, MT or no preference). Other outcome measures include disability (Headache Impact Test questionnaire (HIT-6)) [30], allodynia (allodynia questionnaire) [31], pressure pain thresholds [32] and neck flexor muscle endurance [33] (see later for details). Figure 2 shows all outcome measures and assessments.

**Fig. 2 Fig2:**
[figure not shown]
Schedule of outcome measures and assessments. HIT-6, Headache Impact Test

### Randomization

After baseline measurement, randomization will take place with a 1:1 allocation ratio. An independent statistician who has no involvement with the clinical investigators will generate a random sequence of numbers before the start of the study. The research assistant who is blinded for the randomization sequence will supply sealed and numbered envelopes. In the presence of another administrative assistant, the participant will open the sealed envelope, and an appointment will be made for treatment by either the participating GP or a manual therapist. Participants will be invited to a parallel cohort study if a strong preference for MT treatment keeps them from agreeing to randomization.

### Blinding

Allocation of participants is concealed from the researcher and the research assistant who performs all of the measurements. An independent statistician will carry out the statistical analysis and review the interpretation of the results. For obvious reasons, participating patients, GPs and manual therapists cannot be blinded to treatment.

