### Usual care

Participants assigned to the usual care group will be treated by their general practitioner (GP). The GP will treat participants as usual, based on the recommendations of the practice guideline for headache of the Dutch College of General Practitioners [34]. The GP provides lifestyle advice and, if necessary, prescribes medication. The recommended treatment consists of acute medication for a single attack or prophylactic medication when the migraine attacks occur two times a month or more [5]. The GP will evaluate the treatment in consecutive appointments. Participating GPs will be informed about the research protocol by the researcher during a 1-h meeting.

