### Intervention

The multimodal manual therapy (MT) treatment aims at restoring cervical function in order to reduce nociceptive cervical afferent output. The treatment will include manual pressure techniques on the trapezius muscle and upper cervical/suboccipital musculature to decrease neck pain intensity and cervical muscle tenderness [35]. Neck muscle strength will be trained, by giving low-load craniocervical muscle exercises and correcting sitting and standing postures [36]. The selected spinal mobilizations are low and high-velocity techniques of the cervical and thoracic spine. To create a protocol that will be feasible for all participants, no high-velocity thrust manipulations of the upper cervical region (C0–C3) will be applied in the study, due to possible individual risk factors associated with serious adverse events [37, 38].

Experienced manual therapists will be trained in the treatment protocol prior to the study. The treatment protocol provides recommendations of techniques that can be used; the treating manual therapist decides which techniques will be included, depending on the condition of the participant. The applied techniques will be documented for each session on an evaluation form. Instructions on posture and home exercises will be provided to the participants in booklets. The MT intervention will consist of a maximum of nine sessions of 30 min each, starting with treatment once a week, followed by once every other week during 12 weeks.

During the 12 weeks of treatment, participants will be asked not to make use of additional therapies or medication for their migraine. At all follow-up measurements, possible use of additional therapies and medication will be asked for and registered.

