### Secondary outcome measures

The secondary outcome measures are as follows:
Number of migraine attacks per 4 weeks, recorded in a headache diary during the 4 weeks before follow-up measurements [9]. Migraine attacks will be considered separate attacks if 48 h without headache is reported in the headache diary.Intensity of migraine, assessed on an 11-point numerical rating scale (0 = no pain, 10 = most severe pain) [39].Intensity of neck pain, assessed on an 11-point numerical rating scale (0 = no pain, 10 = most severe pain) [39].Medication use as number of doses per 4 weeks of simple analgesics (e.g., paracetamol), NSAIDs, acute migraine medication (triptans and ergotamines) or prophylactic medication. Participants are asked to report changes of medication to the research assistant at all follow-up measurements.Responder rate will be measured by the number of migraine days before vs. after treatment, dichotomized into ≥ 50% reduction or not [9].Disability, assessed by the HIT-6 questionnaire. The HIT-6 questionnaire consists of six questions measuring pain intensity, social functioning, role functioning, vitality, cognitive functioning and psychological distress on a 5-point ordinal rating scale (never to always). Internal consistency is considered high (Cronbach’s α = 0.82–0.90) and test–retest reliability is fair (ICC = 0.77) [30]. The Dutch version of the HIT-6 questionnaire has shown to be a valid and reliable tool to measure the impact of migraine [40].The endurance of the neck flexor muscles will be scored as the number of seconds the participant can raise his head from the table when lying in a supine position, as described by Harris et al. [33]. Harris et al. reported good to excellent intra-tester reliability (ICC = 0.82–0.91) and moderate inter-tester reliability (ICC = 0.67–0.78) [33].Cutaneous allodynia (CA) will be evaluated with the 12-item allodynia symptom checklist. This questionnaire consists of 12 questions about cutaneous hypersensitivity in the cervical cephalic region. The participant can score yes, no or not applicable. Allodynia symptoms and score on CA severity are defined in the following categories: none (0–2), mild (3–5), moderate (6–8) and severe (9 or higher) [31].We will perform algometry, by measuring pressure pain thresholds (PPTs) with a Wagner FDK algometer at the upper trapezius muscle (at the midpoint between C7 spinosus and the acromion), the suboccipital muscles and the anterior tibial muscle. The PPT measurement will be repeated three times at each point, and a mean score will be calculated. Algometry has demonstrated excellent intra-tester reliability (upper trapezius test–retest ICC = 0.83, 95% CI 0.69–0.91), and excellent inter-tester reliability (upper trapezius ICC = 0.89, 95% CI 0.83–0.93) [32].Participants will be asked to report the global perceived effect on a 7-point rating scale (0 = much worse to 6 = much better). Disability due to attacks will be assessed on a 5-point rating scale (0 = no disability and no medication to 4 = fully disabled even with medication). Also, use of healthcare resources and absence of work will be reported.All adverse events will be administrated for both treatments at all follow-up measurements.

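### The research assistant who should stay blind is told of medication changes at every follow-up, which is likely to disclose allocation for some participants before two assessor-taken secondary tests

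*Protocol article*

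**What the plan says.** On blinding, the Blinding section of the protocol article says: "Allocation of participants is concealed from the researcher and the research assistant who performs all of the measurements". The Methods text under Fig. 1 adds: "All measurements will take place with a trained research assistant at one location". That sentence stands in the paragraph on the parallel cohort, which describes measurements in the cohort and the trial as identical.

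On what is asked at follow-up, the Secondary outcome measures section says: "Participants are asked to report changes of medication to the research assistant at all follow-up measurements". The Intervention section says: "At all follow-up measurements, possible use of additional therapies and medication will be asked for and registered". Adverse events are handled in the same way: "All adverse events will be administrated for both treatments at all follow-up measurements". Healthcare use is also listed, without timing or collector: "Also, use of healthcare resources and absence of work will be reported". The Data collection section limits data access to the researchers and the research assistant.

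On how the arms differ, the Usual care section says: "The GP provides lifestyle advice and, if necessary, prescribes medication". The Intervention section asks participants to refrain from additional migraine therapies and medication during the 12 weeks of treatment.

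**The concern.** One section promises that a named person does not know the allocation. Another directs to that same person information that tends to differ by arm. This is a stated procedure working against a stated property of the design, so the point does not rest on something the article leaves out.

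At stake are the two outcomes that the assessor takes with an instrument or a timer: pressure pain thresholds and neck-flexor endurance. The Background uses sensitization and cervical dysfunction to explain why manual therapy might work, so these two outcomes carry the mechanistic argument. A between-arm difference in them is harder to interpret if the assessor knew the arm for some participants.

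**Working it through.** No figure in the plan is at issue, so the check sets the passages side by side.

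1. **Same person, same visit.** The Blinding section gives all measurements to the research assistant. The medication sentence names the research assistant as recipient, at all follow-up measurements (weeks 12, 26 and 52). For this item the overlap is explicit. The sentences on additional therapies and adverse events give the same timing but no collector. That the assistant collects them is an inference from all measurements being assigned to that person.

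2. **Is the information related to arm?** Entry requires attacks at least twice a month (Inclusion criteria). The Usual care section describes prophylactic medication as recommended at that same frequency. Anyone on prophylaxis at entry must have been stable for 3 months. Participants are asked not to add migraine medication during treatment; the request stands in the Intervention section, and the article does not say whether it covers both arms. A drug newly started by week 12 therefore points towards usual care. Soreness after neck treatment would point towards manual therapy, and a drug side effect towards usual care. A participant with nothing to report discloses little or nothing.

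3. **When does the knowledge act?** Baseline precedes randomization and cannot be affected. The exposed follow-up visits depend on how the items are collected:
   - questions before tests: all 3 visits (weeks 12, 26, 52);
   - tests before questions, same assistant: 2 of 3 visits (weeks 26 and 52), because what is learned at week 12 is carried forward;
   - items collected elsewhere and hidden from the assistant: none by this route.

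   Data access is a second route, since an assistant who can open earlier entries can learn the arm between visits.

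4. **Which outcomes are exposed?** Algometry and the endurance test are. Migraine days, the primary outcome, come from a diary that the participant keeps, so the assessor's knowledge does not enter them.

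5. **How large could the bias be?** For one test at one visit, the spurious between-arm difference is roughly

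   bias = p(MT) × s(MT) − p(UC) × s(UC),

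   where p is the share of an arm (MT, manual therapy; UC, usual care) whose allocation the assessor knows, and s is the average shift in the reading when it is known. The document gives none of the four quantities, so the calculation stops here.

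**The case against.** The strongest case on the other side has four parts.

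- **Only one route is explicit.** The assistant is named for medication changes alone. Electronic capture in Castor leaves room for participant-completed items. This stands, and the other items are treated here as likely routes only.
- **A medication change is not proof of arm.** Participants on stable prophylaxis may enter, and follow-up runs 52 − 12 = 40 weeks beyond treatment, so drugs may change in either arm. This also stands. A reader might infer that the visits reveal every allocation or defeat the blinding, but the document supports only likely disclosure for some participants.
- **The full protocol may hold safeguards.** Test order and instructions not to disclose are details an article commonly leaves out, and the schedule figure is not shown. Their absence is therefore no finding. The sentence sending medication reports to the assessor is in the text and remains.
- **The reach is small.** Two secondary outcomes are involved, and both also depend on participants who know their treatment. This is correct.

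Two further inferences are tempting and fail. The first takes the inter-tester ICC for endurance (0.67–0.78) and reads 1 − 0.78 = 0.22 to 1 − 0.67 = 0.33 as the share of variance open to assessor influence. One minus an ICC measures unreliability, including participant variation and random error, and says nothing about a difference between arms. With one trained assistant at one location, the intra-tester range (0.82–0.91, so 0.09–0.18) would be the nearer figure, and the same limit applies to it.

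The second holds that the phrase "This study is a single-blinded, multicentre, pragmatic clinical trial with two parallel groups" overstates protection of the primary outcome. The Blinding section says that patients, GPs and therapists cannot be blinded, the Discussion lists this as a limitation, and the primary outcome is described as recorded by the participant. Nothing is concealed there.

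**Conclusion.** The concern holds in a limited form. The medication-reporting sentence works against the blinding statement, and the other follow-up items and the assistant's data access probably add to the risk. Allocation is likely to become known for some participants before pressure pain thresholds and neck-flexor endurance are taken, at the same visit or at weeks 26 and 52 by carry-over.

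The size of any resulting bias cannot be derived from the document. The primary outcome, the sample size and the main conclusion are untouched. The verdict assumes that usual-care participants start new medication more often than manual therapy participants do, as the arm descriptions suggest, and that the full protocol does not already route these items away from the assessor. If it does, correcting the one sentence in the article is enough.

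**What to change.** The items should be moved, not dropped: the per-protocol exclusions in the Statistical analysis section depend on knowing who used additional care.

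- Amend the medication sentence so that medication changes, additional care, healthcare use, adverse events and global perceived effect go on a participant-completed form that the assessor cannot open, and restrict the assistant's data access to match. Alternatively, have these items collected by the administrative assistant who, under Randomization, is present when the envelope is opened. This is the part that protects weeks 26 and 52.
- Do algometry and the endurance test first at every visit. On its own this protects only week 12.
- Ask participants not to mention their treatment to the assessor.
- After testing, record whether the assessor knows the allocation or, if not, what the assessor guesses. This shows how often disclosure occurred.

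The cost is a changed access setting, one extra field and occasional follow-up calls where a self-reported adverse event is unclear. Using the administrative assistant adds some of that person's time but no new post.
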